#### Eating disorder symptoms

Individuals with eating disorder symptoms, such as binge eating, may have more difficulty losing weight [59] and hence this will be controlled for in our analyses. Eating disorder symptoms are measured by the Eating Disorder Examination Questionnaire [60]. Acceptable internal consistency and test–retest reliability have been demonstrated for this questionnaire [61]. It has 36 items and measures concerns about shape, weight and eating; restraint and self-reported binge eating. Subscale scores for shape, weight and eating concerns and restraint range between 0 and 6. A higher score indicates more severe eating psychopathology.

#### The Grazing Questionnaire

The Grazing Questionnaire [62] is used to measure the participants’ food grazing behaviours, i.e., to assess whether there is a pattern of continual overeating. Grazing is increasingly recognised as an important eating behaviour associated with obesity [62]. This questionnaire has been validated in a university sample of both genders and has demonstrated high internal consistency, test–retest reliability and convergent validity at initial testing [62].

#### Habit clusters

Habit clusters are measured by the Modified Self-Reported Habit Index [63]. Research has shown that when cognitive resources become limited, individuals are inclined to make heuristic-based choices [64]. This is reflected in obesity-maintaining dietary habits. Given the habitual nature of eating and the rapidity with which people make eating decisions [64], the behaviours are likely to be the consequence of automatic responses to contextual food cues, many of which lead to increased caloric consumption and poor dietary choices [65, 66]. This index has been shown to be a valid and reliable scale to measure physical activity habits [67]. For the purposes of this study, this index has been modified to include other obesity-related behaviours such as sedentary behaviours, smoking and alcohol consumption.

#### Emotion dysregulation

Emotion dysregulation is measured by the Difficulties in Emotion Regulation Scale (DERS) [68]. Emotion regulation has been described as a continuous, dynamic system responsive to all emotional experience, consisting of both autonomic and controlled processes [69, 70], perhaps mediated by executive function [48]. Since it relates to obesity, problems in attentional and inhibitory control have been associated with binge eating and eating pathology in adults [71]. The DERS is a 36-item self-report questionnaire that assesses clinically relevant difficulties in emotion regulation (with a particular emphasis on negative emotions). There is evidence to support the reliability of DERS scores. Specifically, DERS scores have been found to demonstrate good test–retest reliability [72] and the overall DERS score and subscale scores have been found to have high internal consistency within both clinical, for example [68, 73], and nonclinical populations, for example [68, 74]. Support for the construct and predictive validity of DERS scores within both clinical and nonclinical populations has also been found, for example [69].

#### Health-related quality of life

HRQoL is measured with the 12-item Short Form [75], which is a widely used quality of life measure with good construct and criterion validity and with adequate sensitivity to change.

### Behavioural weight-loss group intervention

The BWLT in this RCT targets diet and exercise through behavioural modification techniques over three 90-minute weekly sessions. In the first session, obesity-related risk awareness, challenges with perceived barriers and perceived personal control are discussed in depth. Cognitive challenging techniques are taught and in-session goal setting practices are conducted. In the second session, participants receive comprehensive education about nutrition, hunger management and healthy eating practices. Problem-solving techniques are taught so that participants can effectively deal with difficult situations that threaten their weight-control efforts. National physical activity guidelines are discussed and further training given on goal setting and goal achievement. In this last session, attention is given to motivation enhancement and relapse prevention strategies to help individuals maintain their weight loss.

### Cognitive Remediation Therapy for Obesity

CRT-O is a manualised intervention that consists of mental exercises aimed at improving cognitive strategies, thinking skills and information processing through practice. CRT, in particular, promotes reflection on thinking styles, develops metacognition and helps to explore and apply new thinking strategies in everyday life. The primary function of CRT is to improve the thinking process rather than the content [76–78]. In the absence of a published manual, a CRT-O manual was developed to meet the needs of the obese participants for the purposes of this RCT. The intervention is conducted face-to-face and delivered by the first author (JR), who is a registered clinical psychologist in Australia. The principles, structure and main components of the original CRT-AN are maintained. Some important modifications, however, have been made to adapt the manual for obesity and these are described in Smith *et al*. [25].

### Treatment fidelity

The first author (JR) was trained in a workshop on CRT-AN by the developers of this treatment approach ([name] and [name], Institute of Psychiatry, King’s College London, UK). The third author (ES) piloted the different versions of manualised CRT-O with three people. Concomitant interventions outside of the trial setting are neither encouraged nor prohibited during the intervention phase. To increase transparency and documentation as well as for quality and treatment fidelity assessment, 10% of the sessions will be audiotaped.

### Data collection, management and analysis

Data is collected at baseline, end-of-treatment and the 3-month follow-up by the trial therapist. An independent assessment, blind to intervention group, will be made at the 1-year follow-up. Data is entered, cleaned and coded by a research assistant, blind to group allocation, and stored at a secure university facility according to university protocols. An independent statistician will conduct all preliminary analyses. The Statistical Package for Social Sciences (SPSS) statistics will be used.

Neuropsychological measures will first be examined independently and will then be integrated in an executive function composite following the procedure recommended by Rosnow and Rosenthal [79, 80] and applied by Clark *et al*. [81]. The composite score will be generated by converting each executive function scale across all assessment points to *z*- scores, and then averaging across the measures.

Descriptive statistics will be used to present demographic and clinical data including eating disorder features. Baseline univariate between-group tests will be used to compare outcome variables and clinical and demographic data for the groups. Data will be analysed following the intention-to-treat principle. Linear mixed effects modelling [82] will be used to test for between-group differences in the continuous outcome measures, namely the composite scores of cognitive function, waist circumference and BMI, and potential confounds (e.g., levels of depression, anxiety, stress and emotion dysregulation). Generalised estimating equations [83] with a logit response function, or logistic regression, will be used for dichotomous outcomes, such as achieving a 5% reduction in body weight. Effect sizes between and within the two groups will be calculated with Cohen’s *d* computed with the pooled standard deviation, and the odds ratio will be presented where appropriate.

### Ethics and dissemination

The study has been approved by the Human Research Ethics Committee of the University of Western Sydney (H9787). Written informed consent has been obtained from each subject after thorough information about the study was provided. Participants were advised that all data collected will be de-identified prior to analysis and stored securely in electronic and paper forms. All identifying information (e.g., signed consent forms) will be kept separate from other data and will be held in confidence. Only investigators and authorised research personnel will have access to the data. The results will be submitted to peer-reviewed scientific publications, presented at national and international scientific meetings, presented to relevant community fora and released in lay synopsis form to media outlets.

## Discussion

Obesity is an important global public health issue. Due to the long-term failure of interventions for obesity, there is a desperate need to develop novel and innovative approaches to treatment. In particular, weight-loss maintenance remains a major challenge. Obese individuals are known to suffer from significant cognitive deficits, especially in executive function. We have identified the possibility that an intervention such as CRT could improve treatment outcomes and has the potential to improve current therapy practices.

The application to CRT for obesity is highly novel. Executive function deficiencies in the obese are a potential target and unlike other contributing factors (e.g. diet and exercise) have not previously been investigated. CRT-O, which aims to improve specific deficiencies such as inflexibility, poor problem-solving and poor attention to detail (central coherence), could have benefits for the health of the increasing number of obese individuals in our community and reduce the economic burden from obesity and its medical and psychological sequelae. Our study is designed to compare two groups, a BWLT and CRT-O group with a BWLT and no-treatment group, to allow us to draw conclusions about the specific efficacy of CRT-O following BWLT training compared to no treatment.

The strengths of our study design include adequate concealment of randomised group allocation, use of validated and standardised assessments, and independent blinded data analysis. A limitation is that follow-up assessments are blinded only at 1 year. However, this is an important outcome time, since to be clinically meaningful for longer-term weight-loss maintenance, improvements in cognition need to be sustained over time. Furthermore, the Institute of Medicine has defined criteria for assessing successful weight maintenance as a weight loss of ≥5% of body weight that is maintained for at least a year [84]. For the purposes of this study, the Institute of Medicine’s criteria will be used as a standard definition of successful weight maintenance at this study's 1-year follow-up. Another limitation is that therapeutic time with a therapist is not matched between conditions and participants are not blind to condition, i.e., we are not employing a control–therapy comparison. As obesity tends to get worse without treatment, at our 1-year follow-up, we will examine whether individuals’ BMI is significantly higher in the no-treatment group compared to the CRT-O group. We will also control for any additional treatment each group received in that time and whether the change of executive function predicted that weight loss.

The design of this RCT offers a pathway to address, for the first time, the integral aspects of executive function and its impact on obesity, and their interaction with other maintaining factors such as emotion dysregulation, depression and habitual cluster behaviours. It is hoped that the findings of this RCT will provide an important first step towards an understanding of the potential of CRT in obesity. Based on the limited success of current behavioural weight-loss programmes and coupled with the data on the executive function deficiencies in obesity, it appears likely that improving an individual’s executive function has the potential to enhance treatment outcomes for obesity.

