## Methods/Design

### Participants

First, 90 obese individuals are recruited via direct advertisement to the community in Sydney, Australia. Inclusion criteria are: BMI ≥30 kg/m^2^, age 18 to 55 years, current weight under 180 kg, ability to provide informed consent and having completed 10 years of education in English. Participants who are depressed, have a binge eating disorder, are currently on psychotropic medication, have hypertension (medicated or not medicated), type 2 diabetes, or high cholesterol are eligible. Participants are excluded if they have a history of psychosis, head injury, neurological disorder including degenerative or inflammatory conditions or stroke, attention deficit hyperactivity disorder, epilepsy, developmental or intellectual disability; are unable to complete the testing (e.g. due to hearing, vision or language impediment); are on regular sedative or stimulant medication; and/or report regular substance use or abuse (for alcohol, more than two standard drinks five times a week). Individuals are also be excluded if they regularly use sedatives, hypnotics, antipsychotics, or anti-cholinergic or cholinergic medication. The sample size of 45 per group has been determined based on power estimates using Cohen’s tables for an estimated effect size of 0.6, power of 0.8, one-tailed test, *P* <0.05 and attrition of 20%. Although there are no previous studies of adults with obesity, these levels are commensurate with those achieved by Verbeken *et al*. [12].

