### Psychological assessment

The Clinical Obesity Maintenance Model [48] proposed by Raman and colleagues argues that psychological variables, such as habitual cluster behaviours, emotional dysregulation and mood, interact with executive functioning and impact on the overeating and binge eating behaviours of obese individuals. Hence, the following measures are included in this RCT to investigate the broader range of maintaining mechanisms, including but not limited to executive deficits, and to ensure both groups are equivalent at baseline in other measures that may impact on weight.

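### The 1-year BMI test is worded as a comparison of levels and no model names the outcome's own baseline value; adjusting for it is a free gain, and the baseline significance tests can go

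*Protocol article*

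**What the plan says.** Four places in the protocol article bear on this.

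- **Discussion.** At 1 year the investigators will examine whether "BMI is significantly higher in the no-treatment group compared to the CRT-O group". Neither a change score nor a baseline term is mentioned.
- **Data collection, management and analysis.** Linear mixed effects modelling "will be used to test for between-group differences in the continuous outcome measures", which are listed as the cognitive composite, waist circumference and BMI. No group-by-time contrast and no baseline covariate are named. The same section states: "Baseline univariate between-group tests will be used to compare outcome variables and clinical and demographic data for the groups".
- **Psychological assessment.** Further questionnaires are included partly "to ensure both groups are equivalent at baseline in other measures that may impact on weight".
- **Assessment and Procedure.** All measures are taken at baseline, after 7 to 9 weeks, at 3 months and at 1 year. The baseline assessment comes before the group weight-loss sessions, and randomisation follows the third session.

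The article does name variables to control for: pre-morbid IQ, eating disorder symptoms and further obesity treatment. The baseline value of the outcome is not among them.

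**The concern.** Participants enter at any BMI from 30 kg/m² upwards, with weight limited only to under 180 kg. Most of the spread in 1-year BMI will therefore be differences between people that were there at entry. A comparison of 1-year levels leaves that spread in the error term and any chance baseline imbalance in the estimate. The baseline value of the same outcome is usually its strongest available predictor, and here it is already scheduled.

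The baseline tests do not help. Under proper randomisation any difference they find is due to chance, and a non-significant result does not show that the arms are alike. Whether to adjust should be decided in advance from the expected correlation, not from those results.

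At stake is precision at no cost: potentially a lot for BMI if levels are compared, and some for the composite even if changes are compared.

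**Working it through.** **Inputs from the article (Participants).** "The sample size of 45 per group has been determined based on power estimates": an "estimated effect size of 0.6", power 0.8, a "one-tailed test", and a significance level and loss given as "<0.05 and attrition of 20" per cent. Evaluable per arm: 45 × 0.8 = 36.

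**Assumed inputs.** The article gives neither r nor the BMI standard deviation (SD). I use ranges for both, take the SD as equal at the two visits, and read 0.6 as a difference in units of the unadjusted SD.

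**1. The plan's own figure.** n = 2(1.645 + 0.842)²/0.6² = 34.4, so 35 per arm, and 35/0.8 gives 44. The one-sided t-test needs 35.04, so 36, and 36/0.8 = 45. The stated 45 per group is reproduced.

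**2. Standard error relative to a comparison of follow-up levels.** With the baseline value as covariate (ANCOVA) the ratio is √(1 − r²). For change from baseline it is √(2(1 − r)).

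| r | baseline as covariate | change |
|---|---|---|
| 0.3 | 0.95 | 1.18 |
| 0.5 | 0.87 | 1.00 |
| 0.7 | 0.71 | 0.77 |
| 0.8 | 0.60 | 0.63 |
| 0.9 | 0.44 | 0.45 |
| 0.95 | 0.31 | 0.32 |

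The covariate halves the standard error when √(1 − r²) = 0.5, that is at r = √0.75 = 0.866.

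**3. BMI in kg/m².** With an assumed SD of 6, the standard error of the raw difference is 6 × √(2/36) = 1.41. Adjusted, it is 0.85, 0.62 or 0.44 at r of 0.8, 0.9 or 0.95. For SDs of 5 and 7 the raw figures are 1.18 and 1.65, and at r = 0.9 they become 0.51 and 0.72.

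The difference detectable with 80% power, one-tailed, is (1.645 + 0.842) times the standard error. For SD 6 that is about 3.5 raw and 1.5 at r = 0.9. For scale, a 5% weight loss is 1.5 kg/m² at BMI 30 and 2.0 at BMI 40. The article uses 5% as a threshold for individual success, not as a target difference between arms.

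**4. Composite, d = 0.6, 36 per arm.** Power = Φ(0.6/(ratio × √(2/36)) − z), where 0.6/√(2/36) = 2.546 and z is 1.645 one-tailed or 1.960 two-sided (normal approximation).

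| Analysis | one-tailed | two-sided |
|---|---|---|
| Levels | 81.6% | 72.1% |
| Covariate, r = 0.3 | 84.7% | 76.1% |
| Covariate, r = 0.5 | 90.2% | 83.6% |
| Covariate, r = 0.7 | 97.3% | 94.6% |

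The t-test gives 80.9% and 70.9% for levels. Two-sided power reaches 80% at r of about 0.42. A change contrast has two-sided power of 57.6%, 72.1% and 90.8% at r of 0.3, 0.5 and 0.7, below the covariate analysis each time and below the level comparison at r = 0.3.

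**The case against.** The strongest reply is that the Discussion sentence is narrative and sits among the limitations. The specification is in the analysis section, which gives BMI a mixed model. Baseline is one of the measurement points, the composite is standardised across all assessment points, and several outcomes are framed as change or weight loss. If the model includes baseline and the effect is group by time, baseline is already used, and for BMI a covariate then adds almost nothing (0.44 against 0.45 at r = 0.9). A condensed article may leave such model terms to the analysis plan.

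Much of this stands, and it rules out several stronger readings that a reader might infer:

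- **That BMI will be analysed as an unadjusted comparison of raw values.** The article never says so; it leaves the model's use of baseline open.
- **That the treatment estimate is a group main effect diluted by the baseline visit.** No passage says which model term will be read.
- **That baseline tests replace adjustment, or are the means of ensuring equivalence.** The Psychological assessment section mentions no test, and control for other covariates, including IQ, is planned separately.
- **That adjustment must more than halve the BMI standard error.** That needs r above 0.866; at r = 0.8 the reduction is 40%.
- **That power for the composite has been lost.** On the one-tailed basis of the sample size, 36 per arm gives about 81%. The figure of 71% to 72% comes only from substituting a two-sided test.
- **That a given number of false imbalances will appear.** The article does not say how many baseline tests there will be.

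Two things survive. The Discussion wording and the baseline tests are explicit statements, not omissions. And for the composite, the covariate analysis beats even a group-by-time change contrast unless r is very high (0.87 against 1.00 at r = 0.5).

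**Conclusion.** The point holds as an improvement to the analysis, not as an error that invalidates it. As worded, the 1-year BMI question compares levels, the mixed model is not tied to the outcome's baseline value, and the planned baseline tests serve no useful purpose after randomisation.

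The size of the gain depends on r and on what the mixed model turns out to do. For BMI it is large if levels are compared and slight if changes are. For the composite it is about 3 to 16 percentage points of one-tailed power over a level comparison, for r between 0.3 and 0.7. Both r and the BMI SD are assumptions. The sample size is reproduced, and no shortfall is claimed on its own terms.

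**What to change.** In the analysis section and the Discussion, state that the 1-year and other arm-by-visit contrasts for BMI, waist measures and the executive function composite come from the mixed model in one of two forms:

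- post-randomisation visits as outcomes, with the baseline value of the same outcome as covariate; or
- all visits as outcomes, with the baseline mean constrained equal across arms.

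Reword the 1-year BMI sentence to refer to that adjusted contrast. Present baseline data descriptively by arm and delete the baseline between-group tests. Where the gain in precision is described, give it as a range over assumed r.

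The cost is wording only. Baseline is scheduled for every measure and precedes randomisation, so it is a legitimate covariate. The Trial status section reports data collection still in progress, so the change can be fixed before analysis.

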## Trial status

Recruitment is now complete; therapy and data collection are in progress.

## Abbreviations

BMI: body mass index
BRIEF-A: Behavior Rating Inventory of Executive Function, Adult Version
BWLT: Behaviour Weight Loss Treatment
CRT: Cognitive Remediation Therapy
CRT-AN: Cognitive Remediation Therapy for Anorexia Nervosa
CRT-O: Cognitive Remediation Therapy for Obesity
DERS: Difficulties in Emotion Regulation Scale
HRQoL: health-related quality of life
RCT: randomised controlled trial
WCST: Wisconsin Card Sorting Test.
